**Methods:**

In this multicenter, large-scale, single-blind, randomized controlled trial, we will recruit 252 patients with hypertension and cognitive impairment from 3 hospitals and randomly assign them to 3 groups in a 1:1:1 ratio: the electroacupuncture group, the sham electroacupuncture (SEA) group, and the waiting list group. The electroacupuncture group and SEA group will receive either electroacupuncture or SEA for 12 weeks, while the waiting list group will not receive acupuncture treatment for the first 12 weeks. The primary outcome will be the changes in overall cognitive function, as measured by the Montreal Cognitive Assessment. The secondary outcomes include blood pressure status, subdomain cognitive function, mental status, sleep quality, hemodynamics, and microcirculation indicators.

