## Methods

### Trial Design

This is a multicenter, open-label, waiting list control randomized controlled trial. A total of 252 eligible participants will be randomly assigned in a 1:1:1 ratio to the electroacupuncture group, the sham electroacupuncture (SEA) group, and the waiting list group. The assessments of clinical outcomes will be performed at baseline, week 12, and week 24. Acupuncture treatment was administered once every other day, 3 times per week, for 12 weeks, followed by a 12-week follow-up. The flowchart and study design schedule are shown in Figures 1 and 2, respectively.

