### Participants and Recruitment

We will recruit participants in the outpatient departments of 3 hospitals, including the First Teaching Hospital of Tianjin University of TCM, the TCM hospital of Sichuan Province and Hospital of Chengdu University of TCM, the Affiliated Sichuan Provincial Rehabilitation Hospital of Chengdu University of TCM, and Tianjin Medical University General Hospital. Patients with HTMCI and healthy participants who are interested and whose initial screening meets our recruitment needs will be fully informed of the entire study procedure, benefits, and risks. Clinical trial communicators will fully explain the trial to patients before the trial begins to ensure that all the patients participate voluntarily and sign an informed consent form.

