### Randomization and Blinding

A total of 252 eligible patients will be randomly allocated to the acupuncture group, the sham acupuncture group, and the waiting list group at a 1:1:1 ratio. An independent professional statistician, uninvolved in the trial’s implementation or subsequent statistical analysis, will generate the randomization sequence using SPSS (IBM Corp) software. Both the outcome assessor and the statistician will remain blinded to group assignments. Group assignments will be disclosed only after the completion of the statistical analysis.

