### Interventions

All the groups receive standard treatment, including controlling blood pressure, blood glucose, blood lipid, and symptomatic treatment.

In this trial, 0.25×40 mm needles manufactured by HUATO, Suzhou, China, and the SDZ-III electroacupuncture apparatus by Suzhou Medical Appliance, Jiangsu, China, will be used. Interventions in all groups will be practiced by registered practitioners of TCM with at least 5 years of clinical experience in acupuncture. Acupuncturists will be trained in the study protocol and standardized acupuncture manipulations before study initiation.

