### Statistical Analysis

Statistical analysis was performed using SPSS (version 27.0) software. All patients who completed the randomization and received the overall course of treatment were included in the efficacy analysis to ensure the integrity and comparability of the data. For different types of data, the following statistical methods will be used for analysis:

Data types and test methods: ×2 test is used for count data, and Shapiro-Wilk and Levene test are used for measurement data to analyze the independence, normality, and homogeneity of variance of data.Comparison between groups: for normal distribution and homogeneity of variance, 1-way ANOVA with completely random design was used for comparison between groups. If the variance is not uniform, the Kruskal-Wallis rank sum test of the single-factor nonparametric method of completely random design is used for comparison between groups. For the measurement data conforming to the skewed distribution, the Kruskal-Wallis rank sum test of the single-factor nonparametric method of completely random design was used for comparison between groups.Hypothesis testing and significance level: The count data are expressed as a ratio (%) using the chi-square test or Fisher exact test. The 2-sided test method was used uniformly, and the test statistics and corresponding *P* values were recorded. *P*<.05 was used as a criterion for judging significant statistical significance.

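### Three hospitals are stated but four or five are named, and the single-factor comparison omits hospital: a loss of precision, not a bias

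*Protocol article*

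**What the plan says.** **Hospitals.** The Methods part of the Abstract says "we will recruit 252 patients with hypertension and cognitive impairment from 3 hospitals". Participants and Recruitment repeats the number and starts the list: "We will recruit participants in the outpatient departments of 3 hospitals, including the First Teaching Hospital of Tianjin University of TCM". The next entry is "the TCM hospital of Sichuan Province and Hospital of Chengdu University of TCM", and the list ends with "the Affiliated Sichuan Provincial Rehabilitation Hospital of Chengdu University of TCM, and Tianjin Medical University General Hospital".

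**Design and allocation.** Trial Design states "This is a multicenter, open-label, waiting list control randomized controlled trial". Under Randomization and Blinding, an independent statistician "will generate the randomization sequence using SPSS (IBM Corp) software" in a 1:1:1 ratio. That section does not say whether the sequence is stratified by hospital.

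**Analysis.** Under Statistical Analysis, where data are normal with equal variances, "1-way ANOVA with completely random design was used for comparison between groups". Where they are skewed or variances differ, the article names a Kruskal-Wallis test, again with one factor and for a completely randomised design. No section brings hospital or practitioner into a comparison.

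**Standardisation.** The Interventions section says "Interventions in all groups will be practiced by registered practitioners of TCM with at least 5 years of clinical experience in acupuncture" and adds training in the protocol and in manipulation. Data Management and Quality Control adds standard operating procedures and on-site inspections.

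**The concern.** The hospital count is a plain contradiction. A by-hospital table, a hospital term or a stratified list cannot be set up until the true number is known.

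The analysis point is one of method. Hospitals could differ in mean MoCA change: the electroacupuncture group is needled by hand to elicit a sensation, with current set to patient tolerance, and the MoCA is administered by an assessor. A one-way comparison puts any such difference into the error term and leaves chance differences in hospital mix between arms uncorrected. This is not a detail left to a later plan, because the article itself fixes a single-factor test. A later plan with a hospital term would depart from the published method.

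What is at stake is precision in the comparison of electroacupuncture with sham, which has the smallest planned difference from electroacupuncture: 2.83 − 1.97 = 0.86 MoCA points.

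**Working it through.** **1. Count of hospitals.** The stated figure is 3. The entries are: (i) First Teaching Hospital, Tianjin University of TCM; (ii) the Sichuan Province / Chengdu University entry; (iii) the Sichuan rehabilitation hospital; (iv) Tianjin Medical University General Hospital. That makes 4, or 5 if (ii) is two hospitals. The stated 3 is not reproduced.

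**2. Inputs.** From the Sample Size section: 66 evaluable and 84 randomised per arm; SD of MoCA change 1.13 (electroacupuncture) and 1.38 (sham); α = 0.01. Assumed, because the article gives none: number and size of hospitals in the calculation, and the between-hospital SD of MoCA change, τ = 0.3, 0.5 or 0.8. Within-hospital SD σ is taken as 1.38, so σ² = 1.904.

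**3. Chance imbalance if allocation is unstratified.** In 20,000 random allocations of 84/84/84 over four hospitals of 63, at least one hospital's share differed by 10 percentage points or more between electroacupuncture and sham in about 38% (a rerun with another seed gave 37%). The 90th percentile of the largest difference was 14 points.

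In outcome units, the SD of the resulting shift is τ × √[(2/66) × 3/4]:
- τ = 0.3: 0.045 points
- τ = 0.5: 0.075 points
- τ = 0.8: 0.121 points

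The within-hospital standard error of the difference is 1.38 × √(2/66) = 0.240, and the planned difference is 0.86.

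**4. Variance loss if allocation is unstratified.** With hospital shares p, the unadjusted variance exceeds the within-hospital variance by (1 − Σp²)τ²/σ². Adjustment costs roughly (K − 1)/195 for K hospitals, where 195 = 3 × 66 − 3. For four equal hospitals (1 − Σp² = 0.75; cost 3/195 = 1.5%):

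| τ | Gross excess | Net of adjustment cost |
|---|---|---|
| 0.3 | 0.75 × 0.09/1.904 = 3.5% | 2.0% |
| 0.5 | 0.75 × 0.25/1.904 = 9.8% | 8.2% |
| 0.8 | 0.75 × 0.64/1.904 = 25.2% | 23.3% |

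Simulation over three or four hospitals, equal or split 50/25/15/10%, gives a net loss of about 0-3%, 7% and 17-23%. With no hospital effect, adjusting costs about 1-2%.

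**5. Validity of the one-way test.** Simulated one-way ANOVA, four equal hospitals, 66 per arm, 20,000 runs, nominal 5%:

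| Share of variance held by hospitals | Type I error, unstratified | Type I error, stratified |
|---|---|---|
| 5% | 4.9% | 4.5% |
| 10% | 4.9% | 3.9% |
| 20% | 4.9% | 3.3% |

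The mean estimated difference was zero to within simulation error throughout.

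**6. Power, electroacupuncture against sham.** Pooled SD = √[(1.13² + 1.38²)/2] = 1.261. At 66 per arm and two-sided α = 0.01, power = Φ(0.86/[1.261 × √(2/66)] − 2.576) = Φ(1.34) = 91.0%. If hospitals hold a share ρ of that variance, a hospital term replaces 1.261 by 1.261 × √(1 − ρ). Power is then 91.3%, 92.5%, 94.0%, 95.3% and 96.4% at ρ = 1%, 5%, 10%, 15% and 20%.

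**The case against.** The strongest reply is that a one-way test of an unstratified 1:1:1 allocation matches its design. That is correct: chance imbalance in hospital mix is already reflected in the standard error. A reader might infer that hospital differences contaminate the comparison of electroacupuncture with sham. The documents do not support this, since patients are individually randomised and step 5 shows neither bias nor inflated type I error.

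A reader might also infer that allocation was unstratified. The article is silent, and a condensed article may leave stratification to the full protocol. The 38% figure depends on that reading and on equal hospitals of 63, which the article does not state. The need for a hospital term does not depend on it, because step 5 covers both cases.

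The assumed SDs can be challenged as well. At τ = 0.8 hospitals hold 0.64/(0.64 + 1.904) = 25% of the variance, and at 0.5 about 12%. The outcome is a change score, so stable differences in scoring severity largely cancel. Practitioner experience, training, operating procedures and blinded assessors should narrow the differences further. At τ = 0.3 the gain is about the size of the cost. All of this stands and limits the size of the point.

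Finally, a hospital term does not remove operator differences within a hospital, nor does it show whether an effect came from one centre's practitioners. The article does not say how practitioners are assigned to arms, so no claim about operators can be built on it.

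**Conclusion.** Two things hold. The count of 3 contradicts a list of four or five hospitals, and the published analysis of a multicentre trial has treatment group as its only factor.

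The consequence of the second is lost precision only. Without stratification, the variance of the difference between electroacupuncture and sham is about 0-3% to 17-23% larger than it need be over the assumed range of τ. In power terms this is 0.3 to about 5 percentage points for hospital shares of 1% to 20%. With stratification, the one-way test is conservative. These sizes rest on assumed between-hospital variation and hospital sizes; the direction does not, apart from the small cost when hospitals barely differ. The change is worth making because it is cheap and improves a method the article has already fixed. It is not a threat to the trial's validity.

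**What to change.** 1. Correct the hospital count or the list so that the Abstract and Participants and Recruitment agree, and make clear whether the Sichuan entry is one hospital or two.
2. For MoCA change and the other continuous outcomes, replace the one-way ANOVA with a linear model with arm and hospital as fixed factors.
3. Where the article's rank route applies, use a hospital-stratified rank test: van Elteren for a pairwise comparison, or its extension to three groups for the overall test.
4. State whether the allocation sequence was stratified by hospital.
5. Report allocation and the difference between electroacupuncture and sham by hospital, as description only. With four equal hospitals there would be about 16 to 21 patients per arm in each (66/4 to 84/4), too few to judge consistency.

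The Results section says that no analysis has been performed, so the change can be recorded as an amendment before group assignments are disclosed. Each patient's hospital is known, so no new data are needed. The cost is two to four degrees of freedom out of about 195, and about 1-2% in variance if hospitals do not differ. Operator differences within a hospital remain unaddressed.

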### Sample Size

According to the literature [52], acupuncture treatment increased the mean MoCA score by 2.83 (SD 1.13); the mean change in MoCA in the sham acupuncture group was 1.97 (1.38), waiting group, the mean change in MoCA was 0.48 (SD 1.65); the test level was α=0.01; power was 95%; and it was calculated by the PASS (version 15.0; NCSS, LLC) software to obtain a sample size of 66, considering a 20% dropout rate, 84 cases were proposed to be included in each group, and 252 participants were finally included.

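### Kruskal-Wallis is named as the remedy for unequal variances, which it does not correct; on the plan's own SDs it would probably replace the comparison of mean MoCA change that the trial was sized on

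*Protocol article*

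**What the plan says.** The abstract's Methods paragraph defines the endpoint: "The primary outcome will be the changes in overall cognitive function, as measured by the Montreal Cognitive Assessment".

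The Statistical Analysis section starts with pre-tests: "Shapiro-Wilk and Levene test are used for measurement data to analyze the independence, normality, and homogeneity of variance of data". One-way ANOVA is reserved for data that are both normal and of equal variance. For the other cases it says: "If the variance is not uniform, the Kruskal-Wallis rank sum test of the single-factor nonparametric method of completely random design is used". Skewed measurements also go to Kruskal-Wallis. The section names no other method for continuous outcomes, so this rule governs MoCA change. Tests are two-sided at .05, and test statistics and P values are to be recorded. The level of the pre-tests is not given.

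The Sample Size section works from mean MoCA changes of 2.83 (SD 1.13) for acupuncture, 1.97 (SD 1.38) for sham and 0.48 (SD 1.65) for the waiting list, with α 0.01 and 95% power, "to obtain a sample size of 66, considering a 20% dropout rate, 84 cases were proposed to be included in each group".

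**The concern.** Three things in this rule do not fit together.

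- **Wrong remedy.** Kruskal-Wallis tests for a shift in location only when the groups share shape and spread. It is not a correction for unequal spread. The usual mean comparison for that case, Welch's, is not named.
- **Different question.** The trial is sized on mean changes in MoCA points. A rank test asks whether scores in one arm tend to exceed those in another, and it does not itself estimate a difference in points.
- **Unfixed test.** Whether the primary hypothesis concerns means or ranks is settled only once the data are seen. The Sample Size section already expects the unequal SDs that would trigger the change.

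At stake is a primary result that answers a different question from the one planned and, if the data are skewed, may be significant when the mean changes are equal.

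**Working it through.** **Inputs.** From Sample Size: means 2.83, 1.97 and 0.48; SDs 1.13, 1.38 and 1.65; 66 per arm before and 84 after the dropout allowance. From Trial Design: 1:1:1 allocation. Assumed: pre-tests at 0.05, and Levene centred on the mean.

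**Step 1: the plan's own figure.** For two means, n per group = (z_α + z_β)² × (SD₁² + SD₂²) / δ². For acupuncture against sham:
- δ = 2.83 − 1.97 = 0.86, so δ² = 0.7396.
- SD₁² + SD₂² = 1.2769 + 1.9044 = 3.1813, and 3.1813 / 0.7396 = 4.301.
- One-sided α 0.01: (2.326 + 1.645)² × 4.301 = 15.77 × 4.301 = 67.8, so 68.
- Two-sided α 0.01: (2.576 + 1.645)² × 4.301 = 17.81 × 4.301 = 76.6, so 77.

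The stated 66 is close to the one-sided result and is not matched two-sided. A three-group F test at 0.01 needs only 11 to 22 per group, depending on the SD used. For dropout, 66 / 0.80 = 82.5, so 83 against the stated 84. For the present point, what matters is that the inputs are means and SDs of MoCA change.

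**Step 2: the planned spread.** 1.65 / 1.13 = 1.46, and 1.65² / 1.13² = 2.7225 / 1.2769 = 2.13.

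**Step 3: how often ANOVA is abandoned** (simulation with the planning means and SDs).

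| What triggers the switch | 66 per arm | 84 per arm |
|---|---|---|
| Levene alone | 71% | 82% |
| Levene or any per-arm Shapiro-Wilk, continuous normal data | 76% | 84% |
| Levene or a per-arm skewness test, whole-point scores | 76% | 84–86% |
| Levene or Shapiro-Wilk on pooled residuals, whole-point scores | 95% | 98% |
| Levene or any per-arm Shapiro-Wilk, whole-point scores | about 100% | about 100% |

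The last two rows are high because Shapiro-Wilk detects discreteness, not skewness.

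The Levene figure depends on the planning SDs. With SDs of 1.25, 1.38 and 1.51 it falls to 23% at 66 per arm and 27% at 84. With equal SDs it is about 5%.

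**Step 4: rejection at nominal 5% when the means are equal** (planning SDs).

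| Setting | Kruskal-Wallis | ANOVA | Welch |
|---|---|---|---|
| Symmetric, 66/66/66 | 5.2% | 5.3% | 5.0% |
| Symmetric, 80/66/50, most variable arm smallest | 6.1% | 6.8% | 5.3% |
| Skewness 0.5, 66 per arm | 5.2% | not run | 4.6% |
| Skewness 1.0, 66 per arm | 7.8% | not run | 5.2% |
| Skewness 1.5, 66 per arm | 11.8% | not run | 5.0% |

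In the skewed rows Kruskal-Wallis is responding to a real difference in ranks. Unequal spread and skewness together separate the arms in rank although their means agree.

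**Step 5: what a mean comparison would report.** Acupuncture minus sham = 0.86 points. SE = √(3.1813 / 66) = 0.22. The 95% half-width is 1.98 × 0.2195 = 0.43, so the interval is about 0.43 to 1.29 points. Power at two-sided α 0.01 and 66 per arm is 90.6% for Welch and 88.8% for the rank test.

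**The case against.** The strongest defence is that the rule does little damage on the plan's own terms. Allocation is 1:1:1, and with equal arms and symmetric data Kruskal-Wallis holds its level and loses under 2 percentage points of power against Welch. That stands. It also shows that the Levene gate protects against very little, since ANOVA holds its level in the same setting.

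A second defence is that effect estimates, intervals and covariates commonly belong in an analysis plan that is not shown. That also stands. Recording P values does not exclude reporting mean differences, and the ANOVA route as written has no baseline covariate either. So a missing CI or a missing baseline adjustment cannot be blamed on the switch. The choice of Kruskal-Wallis for unequal variances is different: the protocol states it, and an analysis plan could mend it only by departing from it.

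Two stronger readings are tempting and are not supported:
- **That the switch to ranks is near certain on the plan's figures.** This needs whole-point scores, Shapiro-Wilk at 0.05, and a rule that any rejection leads to Kruskal-Wallis. The text sends only skewed data there. Data that are symmetric but not normal fail the ANOVA condition and have no stated route.
- **That unequal spread alone inflates false positives in this design.** It does not with equal arms. The inflation in Step 4 needs skewness or unequal arms as well. Skewness is an assumption that the documents do not give.

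**Conclusion.** The point holds in a limited form. The protocol gives the wrong remedy for unequal variances, and by its own planning SDs a rank test would probably displace the comparison of mean MoCA change: about 71% of trials at 66 per arm and 82% at 84 by Levene alone. These figures assume a 0.05 pre-test level, analysis of change scores, and that the planning SDs are true. The remaining chance of staying with ANOVA is what leaves the primary test dependent on the data.

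The main loss is one of fit and interpretation: the hypothesis tested may not be the one the trial was sized for. The false-positive cost is negligible for equal arms with symmetric data. It reaches roughly 7 to 12% only under assumed skewness of 1.0 to 1.5, where Welch stays near 5%. This does not invalidate the trial, but it should be corrected. The Results section says that no data analysis has been performed, so at the time of writing the change could still be made before results were known.

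**What to change.** Remove Levene and Shapiro-Wilk as gatekeepers. Name one primary comparison of mean MoCA change that allows unequal variances. Either of these would serve:
- Welch ANOVA with Welch pairwise contrasts; or
- a linear model for MoCA with heteroscedasticity-robust standard errors, optionally adjusted for the baseline MoCA that is already collected.

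Report the mean difference in MoCA points with its CI. Keep Kruskal-Wallis as a sensitivity analysis, to be run whatever the distribution looks like, so that the gap for symmetric non-normal data also disappears.

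The cost is a change of wording and, at most, a trivial loss of efficiency if the variances turn out equal. No new data are needed.

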## Results

The study protocol has been approved by the institutional review board of the First Affiliated Hospital of Tianjin University of TCM. This study was registered on April 26, 2024, with the Chinese Clinical Trial Registry. Data collection began in May 2024 and ended in April 2025. Currently, data from this trial are in the collection phase, and no data analysis has been performed. As of January 1, 2025, we have collected data from 65 patients. The results of this trial are expected to be submitted for publication in July 2026.

## Discussion

### Overview

Hypertension is the leading risk factor for the global disease burden, a major cause of cardiovascular and cerebrovascular morbidity and mortality in China, and one of the most prevalent chronic diseases [53]. Microcirculation plays an important role in maintaining peripheral vascular resistance and blood pressure stability. Abnormal microvascular blood perfusion is an early manifestation of hypertension [54]. At the same time, cerebral blood flow regulation disorder and cerebral hypoperfusion have direct influence on cognitive function [13]. Therefore, MD is the common pathophysiological basis of hypertension and MCI.

Clinical findings suggest that TCD markers of cerebral flow regulation in patients with hypertension are strongly associated with cognitive ability, with poorer cognitive function associated with enhanced dynamic brain autoregulation in the middle cerebral artery [55]; The content of NO is closely related to oxidative stress response, which can activate the nuclear factor kappa-light-chain-enhancer of Activated B Cells pathway, and then cause inflammation in vivo, promote the release of proinflammatory mediators in the blood vessel wall, and accelerate the occurrence and development of hypertension and vascular complications; ET-1, as an important substance regulating vasoconstriction, can promote vascular smooth muscle cell proliferation, fibrosis, and inflammation, and has important significance in the pathophysiology of vascular endothelium [56]. All the above can further affect the microcirculation index by affecting the vascular endothelium.

Acupuncture, as a special treatment method of TCM, can regulate blood pressure by regulating the neuroendocrine system, improving metabolic activities, changing gene expression related to blood pressure, and so on [57-59]. At the same time, it has been proved that acupuncture can restore the decreased cognitive function to some extent by regulating the hypothalamic oxidative stress pathway, proinflammatory cytokine [60] and improving the brain white matter injury [61].

